### Timeline

2.4

At the baseline visit, researchers will explain the study and obtain informed signed consent. They will then introduce the patient to REDCap, a secure web platform for building and managing online databases and surveys (https://www.project-redcap.org/). After checking eligibility at baseline, patients will be randomly allocated to one of the two treatment arms by REDCap, using simple randomization. The clinician-administered face-to-face questionnaires will be administered to all patients at this baseline evaluation (T0), while REDCap will send self-administered measures by e-mail at baseline (T0), 3 months (T1), 6 months (T2), and 9 months (T3) (Fig. 1).

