### Power analysis

2.7

The sample size has been estimated using R software, setting a non-inferiority margin of 5 points on the HADS (Vaganian et al., 2020) with a power of 80 % and a one-tailed α of 2.5 %. Assuming a dropout rate of 25 %, we require 152 participants (76 per branch) to ensure a 95 % bilateral confidence interval that excludes the non-inferiority threshold.

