## Discussion

3

The current protocol describes a randomized controlled trial intended to examine whether a stepped-care, eHealth-based psychosocial intervention can effectively detect and address the psychosocial needs of patients with advanced lung cancer. We plan to conduct an open-label randomized controlled trial in two groups: one receiving an individualized online stepped-care psychosocial intervention, and the other group receiving an average of seven face-to-face visits with a clinical psychologist.

Patients with lung cancer are mostly diagnosed at advanced disease stages and have minimal prospect of cure. Such a scenario produces stress and psychological trauma for many patients, which in turn, affects their QoL (Liegey Dougall et al., 2017). Given that effective palliative care should improve the QoL of patients and their families, tackling their psychosocial needs in an efficient manner should be among the top priorities of comprehensive palliative care. Health education (Yu et al., 2022) and psychosocial care (Jansen et al., 2019) can both mitigate the emotional distress of a diagnosis and improve QoL among patients with lung cancer. However, the limited access to such care presents an important barrier (Travado et al., 2017).

The use of eHealth can overcome barriers requiring physical attendance at health centers with symptoms of fatigue, dyspnea, or pain (Rajapakse, 2021). As ICTs have emerged to deliver psychosocial interventions reliably to vulnerable patients with advanced cancer (Penedo et al., 2020), clinicians and researchers have begun to study techniques to deliver palliative interventions in an eHealth format (Chua et al., 2019; Gómez-Batiste et al., 2014). However, existing research has usually centered on physical symptoms, not the emotional and spiritual concerns of patients. Furthermore, patients benefit most from psychosocial interventions when they have elevated baseline emotional distress (Jansen et al., 2019; Medina et al., 2022; Nissen et al., 2021), stressing the importance of individualized strategies that allocate resources to patients with at-risk profiles.

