The first limitation of this study is its focus on patients with advanced lung cancer. This may make it difficult to generalize the current findings to other cancer populations. However, given that it will cover a broad range of psychosocial needs that are shared by all cancer patients, it should be able to serve as a starting point for developing other end-of-life care programs, regardless of the underlying pathology. Other methodological weaknesses include the high risk of dropout and missing data with online questionnaires, especially in this delicate cancer population. To diminish this risk, we have shortened the 1-year follow-up used in similar programs to just 9 months. Also, a health psychologist will closely follow all included patients and help them to complete the online questionnaires by phone when needed. The online questionnaires are also structured so that they begin with the primary outcomes in anticipation that this might facilitate their completion, and in any case, they have been designed to last a maximum of 20 min. Finally, although online treatments are increasingly considered acceptable, age and digital literacy still dictate access to ICT, and by association, the study. To improve digital literacy, the first face-to-face visit will include a digital welcoming session and we will provide a technical support service to all patients, including a video tutorial about how to use the ICOnnecta't application.

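### In this open-label trial, allocation is described before the e-mailed T0 self-reports, and nothing requires T0 to be submitted before the arm is known

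*Protocol article*

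**What the plan says.** Section 2.4 (Timeline) of the protocol article describes the baseline visit in this order: explanation and consent, introduction to REDCap, eligibility check, allocation, questionnaires. On allocation it says: "After checking eligibility at baseline, patients will be randomly allocated to one of the two treatment arms by REDCap, using simple randomization". The next sentence covers the questionnaires. For the interview part: "The clinician-administered face-to-face questionnaires will be administered to all patients at this baseline evaluation (T0"). For the rest: "REDCap will send self-administered measures by e-mail at baseline (T0") and again at T1, T2 and T3. Only the ENP-E is described as interviewer-administered, so I read the self-administered set as including the HADS, FACIT-Sp, DS-II, FACT-L and ARMS-e.

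The Discussion (section 3) adds three facts:

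- Blinding: "We plan to conduct an open-label randomized controlled trial in two groups".
- Length of the online questionnaires: "they have been designed to last a maximum of 20 min".
- Help with them: "a health psychologist will closely follow all included patients and help them to complete the online questionnaires by phone when needed". Nothing says that this psychologist is masked to the arm.

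Section 2.9 describes baseline differences as pre-treatment, not pre-randomisation. It fits multilevel models with time and therapy as predictors and enters their interaction later. It assesses non-inferiority on the HADS by comparing group means at T2 and T3. Section 1.1 expects larger gains in patients with worse baseline results and expects baseline spirituality to predict outcome.

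**The concern.** A baseline score serves as a reference because the arm cannot have influenced it. If the patient already knows the arm when answering, that protection is lost. Here the T0 measures are subjective self-reports, the arms differ visibly (online stepped care against face-to-face sessions), and all participants must have internet access and digital experience. Relief or disappointment at the allocation could plausibly colour a distress score, in a direction that cannot be predicted.

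At stake are the analyses that use T0: the therapy and time-by-therapy terms in the multilevel models, any model that takes T0 as a covariate, the table of baseline differences, and the hypotheses on baseline severity and baseline spirituality. Later analysis cannot fully repair a T0 score given after the arm is known.

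**Working it through.** **Order of events.** Section 2.4 places allocation after the eligibility check and before either questionnaire sentence. It does not state in words that the T0 e-mail follows allocation, or when the patient learns the arm. It also contains no rule that T0 comes first. The text therefore allows arm-aware T0 scores without proving them.

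**Where T0 enters.** Section 2.1 counts four assessments and section 2.9 models time, so I take T0 to be one of four outcome occasions. Let *b* be a shift in mean T0 HADS in one arm caused by knowing the allocation. With complete data and equally spaced occasions coded 0, 1, 2, 3 (mean 1.5, sum of squares 5):

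- Therapy main effect without interaction, averaged over four occasions: bias = *b*/4.
- Change from T0 to T3, time categorical: bias = −*b*.
- Linear time-by-therapy slope: weight on T0 = (0 − 1.5)/5 = −0.3, so −0.3*b* per interval and −0.9*b* over three intervals.
- Outcome adjusted for T0 with slope β: bias = −β*b*.
- Raw difference in means at T2 or T3: bias = 0.
- Difference at T2 or T3 read off a linear-time model: weight on T0 = 1/4 + (0.5)(−1.5)/5 = 0.10 at T2, and 1/4 + (1.5)(−1.5)/5 = −0.20 at T3.

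**Illustrative size.** Neither *b* nor β is in the documents. Assume *b* = 1 point and β = 0.4 to 0.6. The change contrast moves by 1 point and the adjusted contrast by 0.4 to 0.6. Section 2.7 works by "setting a non-inferiority margin of 5 points on the HADS", so these are 1/5 = 20% and 0.4/5 to 0.6/5 = 8% to 12% of the margin. The averaged therapy effect moves by 0.25 points, or 5%.

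**HADS SD.** Section 2.7 gives 76 per arm, 80% power, one-sided α of 2.5% and 25% dropout, but no SD. Evaluable n = 76 × 0.75 = 57 per arm. From n = 2·SD²·(1.960 + 0.842)²/5², SD = 5·√(57/2)/2.802 ≈ 9.5. I use 6 to 9.5 as an assumed range.

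**Chance difference at T0, for scale.** SE = SD·√(2/76). SD 6 gives 0.97, SD 7 gives 1.14, SD 8 gives 1.30 and SD 9.5 gives 1.54. The 95% limits run from ±1.9 (SD 6) to ±3.0 (SD 9.5). This is ordinary sampling variation, not bias. It also means that a test of baseline differences would be unlikely to reveal a 1-point arm-related shift.

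**If non-inferiority were read from a baseline-dependent estimate.** Take a bias of 1 point in favour of eHealth, 57 evaluable per arm and, for simplicity, the SE of a plain difference, SD·√(2/57). One-sided error at the margin = Φ(1/SE − 1.960):

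- SD 9.5: SE 1.78, error 8.1%.
- SD 7: SE 1.31, error 11.6%.

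The planned level is 2.5%. This does not apply to the raw T2 and T3 comparison that section 2.9 states.

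**The case against.** The strongest reply is that the order is inferred. The questionnaire sentence summarises the whole T0 to T3 schedule and need not be the next step after allocation. Patients meet REDCap before allocation, the time of disclosure is not stated, and Fig. 1 is not shown. This stands: the documents do not establish that patients answer T0 knowing their arm. They also do not contain the safeguard, and one sentence would supply it.

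A reader might also infer four stronger things, none of which the documents support:

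- That the non-inferiority conclusion is biased. The stated test compares T2 and T3 means and names neither a change score nor a T0 covariate.
- That simple randomisation leaves baseline distress unbalanced. It balances in expectation. Chance differences are already covered by the confidence interval and can be adjusted for if T0 is sound.
- That failing to get 76 in each arm damages power. Even a 64/88 split, at the edge of the 95% range for 152 patients, raises variance by 2.6%, from (1/64 + 1/88)/(2/76) = 1.026. It lowers power from 80.0% to 79.0% at the back-solved SD. Stratified blocks are an option with their own cost in an open-label trial, because they make allocations more predictable.
- That unreturned T0 forms remove patients from the intention-to-treat analysis. With maximum likelihood and T0 as an outcome occasion, a patient with later scores stays in. Loss would arise only where a model needs T0 values as covariates, and the Discussion describes steps to limit missing forms.

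**Conclusion.** The point holds as a gap in the described sequence. The text puts open-label allocation ahead of the e-mailed self-reports and does not require T0 to be submitted first. If carried out that way, T0 scores could be coloured by the arm. This could bias the therapy and time-by-therapy terms, any T0-adjusted estimate, the baseline comparison, and the baseline-severity and spirituality hypotheses. The raw T2 and T3 HADS comparison would be unaffected.

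The size is unknown. The 1-point shift, the slope of 0.4 to 0.6 and the SD of 6 to 9.5 are my assumptions. Under them the bias is 0.25 to 1 point, or 5% to 20% of the margin, with a sign that depends on the analysis and on which arm shifts. The conclusion also rests on T0 being an occasion or covariate in the models and on Fig. 1 not already fixing a safe order. I rate it a cheap improvement worth making, not a fault that undermines the main comparison.

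**What to change.** State in section 2.4 that patients complete and submit all T0 self-reports in REDCap at the baseline visit, and that REDCap releases the allocation only after submission. If this is already the practice, or Fig. 1 shows it, a clarifying sentence is enough. In section 2.9, describe the baseline comparison as pre-randomisation once that is true.

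The cost is a REDCap setting, a line in the protocol, and a slightly longer baseline visit for forms designed to take at most 20 minutes. The sample size of 152 stays as it is. The change can apply only to patients not yet randomised. If some patients have already been allocated under another order, record for each whether T0 was submitted before or after the arm was known, so that T0-dependent results can be checked in the protected subset.

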### Measures

2.5

Sociodemographic and clinical data regarding cancer characterization will be obtained from two sources: ICO's computerized clinical history system (Patient Care Service, SAP https://www.sap.com/index.html) and semi-structured interviews using the Psychosocial and Spiritual Needs of End-of-Life Patients Questionnaire (ENP-E) (Mateo-Ortega et al., 2019). The ENP-E is a hetero-administered clinical instrument with three subscales: evaluation of psychosocial needs (12 items), exploration of worries (1 item), and external signs of emotional distress (1 item). A score ≥ 28 indicates moderate to severe need and recommends assessment for specialized intervention.

#### Primary outcomes

2.5.1

Hospital Anxiety and Depression Scale (HADS): Assessed emotional distress through 7 anxiety items (HADS-Anxiety) and 7 depression items (HADS-Depression). The range of scores is 0–21 for each subscale, and 0–42 for the overall questionnaire. An overall score ≥ 10 is indicative of moderate emotional distress and ≥ 16 of high emotional distress (Carmen Terol-Cantero et al., 2015).

Functional Assessment of Chronic Illness Therapy-Spiritual Well-Being (FACIT-Sp): Spirituality will be assessed through the Spanish version of the FACIT-Sp (Peterman et al., 2002). This instrument assesses three dimensions of spirituality through two subscales: 1) meaning and peace (8 items), and 2) faith (4 items). The overall score ranges between 0 and 48, between 0 and 32 for the first subscale, and 16 for the second. Higher scores are indicative of greater spiritual well-being.

Demoralization Scale – abbreviated version (DS-II): Patient's demoralization will be assessed through the Spanish version of DS-II (Belar et al., 2019). The DS-II is composed of 16 items, 8 for each of its two subscales: 1) meaning and purpose, and 2) coping. Scores <10 indicate no demoralization, between 10 and 19 moderate demoralization, and > 20 severe demoralization.

Functional Assessment of Cancer Therapy – Lung Cancer (FACT-L): to measure the QoL of LC patients, the Spanish adaptation of the FACT-L will be used (Cella et al., 1998). The FACT-L is an instrument derived from the general cancer QoL questionnaire, FACT-G, with an added subscale specific to LC and its symptoms. It has 36 items organized into 5 subscales: 1) physical well-being, 2) functional well-being, 3) social/family well-being, 4) emotional well-being and 5) LC. Higher scores correspond to a better QoL.

Adherence to Refill and Medication Scale (ARMS-e): Medication adherence will be assessed trough the Spanish version (González-Bueno et al., 2017) of ARMS-e, which is a valid and reliable scale for patients with a chronic disease. This instrument consists of 12 questions: 8 are focused on the patient's consistency in taking medication appropriately and 4 on their proper collection. Lower overall scores correspond to better adherence.

#### Secondary outcomes

2.5.2

Edmonton Symptom Assessment System (ESAS-r): Patients' symptomatology will be controlled through ESAS in its revised version, adapted and validated in Spanish (ESAS-r) (Carvajal et al., 2013). ESAS-r is an instrument that is commonly used both in palliative care and in advanced cancer situations. It has 10 visual numerical scales that assess physical and psychological symptoms. Higher scores are indicative of higher pain/distress. The burden and severity of symptoms may affect other variables analyzed in the study and.

Health education: will be assessed using a visual analogue scale (VAS, 0–10) scoring patients' satisfaction with the health information received during their cancer journey, both physically and emotionally.

##### Cost-utility analyses

2.5.2.1

European Quality of Life Scale (EQ-5D-3L): The EQ-5D, which provides a measure of Health-Related QoL (HRQoL), is helpful for the evaluation of the cost-utility of health interventions (Kennedy-Martin et al., 2020). It will be administered in its Spanish adapted and validated version (Badia et al., 2001). This instrument is composed of three sections: 1) descriptive system, 2) visual analogue scale (VAS), and 3) social value index. The value index ranges from 1 (best health) to 0 (death) and is used alone or in combination with life years for the calculation of Quality Adjusted Life Years (QALYs).

Use of medical care and psychotropic medication: These variables will be assessed through SAP by collecting the number of patients' visits with each health professional (e.g., oncologist, emergency department, social worker, psychiatrist, psychologist, nurse), as well as their prescribed psychotropic medication (i.e., drug, dose, and schedule). Costs will be calculated according to national or institutional rates.

Time off work: the number of sick leave days for each patient will be evaluated through SAP. Costs will be estimated according to national rates.

Professional salaries: The costs of hours that professionals dedicate per week to each treatment arm will be assessed through SAP and institutional rates.

Infrastructure costs: the costs per patient per month required for the development and maintenance of the online platform in the case of the EG, and these costs applied to the hospital infrastructure to ensure face-to-face visits in the case of the CG, will be assessed through each provider (EG: technology provider; CG: hospital management).

Transport costs: an estimate of the cost per patient in using a given type of transport will be obtained based on official mobility data provided at the government level for the metropolitan area of Barcelona.

##### Satisfaction with and usability of the digital platform (only for patients included in the experimental group -EG- ICOnnecta't)

2.5.2.2

Satisfaction: will be assessed using a visual analogue scale (VAS, 0–10) in the EG patients scoring their satisfaction with the online platform used during treatment.

Usability: will be assessed using a VAS (0−10) in the EG patients scoring their perception of the usability of the online platform used during treatment.

##### Early detection of patients at risk of emotional distress and time to receive appropriate psychosocial care

2.5.2.3

Well-being - emotional discomfort screening: it will be evaluated through an emotional state thermometer with a response system in VAS format, which will be scheduled weekly on the ICOnnecta't platform (see Fig. 2).

**Fig. 2 f0010:**
[figure not shown]
Stepped digital psychosocial intervention ICOnnecta’t.

The number of detected clinical cases: in the EG this will be obtained through the number of potential clinical cases recorded throughout treatment (VAS ≥6). In CG it will be obtained through the number of clinical cases recorded in the follow-up of face-to-face visits or if the patient reports a worsening by telephone and the visit is brought forward to confirm if it is a clinical case (VAS ≥6).

Waiting time to provide psychosocial intervention: In the EG, the time between the occurrence of a potential clinical case (VAS ≥ 6) and the start of psychosocial intervention will be assessed. The CG will assess the time between the face-to-face screening visit that confirms the clinical case and the next face-to-face visit.

Percentage of resolved psychosocial cases: in both groups it will be obtained through the number of clinical cases that are resolved.

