### Aims and hypotheses

1.1

The main objective of the project is to implement and evaluate the efficacy of a stepped online ecosystem for detecting, following, and addressing the psychosocial needs of patients with lung cancer and to compare those with usual face-to-face treatment. We aim to detect cases at risk of significant emotional distress and decrease the time to access appropriate psychosocial care when using eHealth and usual face-to-face care.

Comparisons between the two interventions will consider the effects on ameliorating the psychosocial consequences of lung cancer and its treatment on emotional distress, demoralization, QoL, and medication adherence, including consideration of the role of spirituality and patient perception of their health education. The cost-utility of each intervention will then be analyzed in terms of quality adjusted life years (QALYs), considering use of additional health services, consumption of psychotropic drugs, sick leave durations, professional salaries, and infrastructure and transportation costs. We will then measure perceived satisfaction and usability of the eHealth ecosystem. Finally, the cases at risk of emotional distress will be detected earlier than treatment as usual. Consequently, using new technologies, we will decrease the time to access appropriate psychosocial care.

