#### Treatment as usual - psychosocial face-to-face treatment

2.6.2

Patients in the control group will receive standard in-person psychosocial care delivered by a clinical psychologist. This will consist of an average of seven individual sessions, lasting 45–60 min each, with an inter-session spacing of 2–3 weeks. The clinical psychologist will provide the intervention based on individual meaning-centered psychotherapy for advanced cancer patients (Breitbart et al., 2012), aiming to help maintain or enhance the sense of meaning, peace, and purpose in the lives of patients with advanced cancer. Patients in this treatment arm will also have access to the educational materials of level 2 of the eHealth intervention, which will be provided in a freely accessible web portal for all patients and their families.

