### Planned statistical analysis

2.9

Descriptive analyses will be performed using Student t or chi-squared tests, as appropriate. This will include assessment of sociodemographic and clinical variables at baseline, together with any pre-treatment differences between groups. Intention-to-treat analyses will then be performed through multilevel linear models to compare both groups on each primary outcome: emotional distress (HADS), demoralization (DS-II), QoL (FACT-L), and medication adherence (ARMS-e).

The modeling process will be parsimonious and guided by fit indexes, starting with a model using the time and type of therapy as fixed predictors. Then, random effects will be tested, and the interaction between time and type of therapy, the eHealth step reached, symptomatology (ESAS-r), and spirituality (FACIT-Sp) will be progressively entered as predictors. The estimation method will be maximum likelihood. Effect sizes (Hedges' g) will be reported for the primary outcomes and non-inferiority will be assessed for the HADS by comparing the means of both groups at T2 and T3. Additional multilevel linear models will be run to assess changes in health education (VAS) between groups, according to the same procedures. As for the cost-utility analyses, the EQ-5D will be used to compute the QALYs together with associated costs for medical care, psychotropics, sick leave, professional salaries, infrastructure, and transportation.

Descriptive analyses will also be conducted for platform's satisfaction and usability (VAS), as well as for participants reaching each step in the eHealth group. Mean differences in the number of clinical cases detected (according to the emotional thermometer), waiting time to provide care, and number of clinical cases solved will then be compared between groups by Student *t*-tests. For the reporting of results, 95 % confidence intervals will be provided. Analyses will be performed using IBM SPSS version 24 (IBM Corp., Armonk, NY, USA) and R software, with support provided by the biostatistics department of IDIBELL.

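### The between-arm test on the number of detected cases cannot by itself show better detection, because the count also rises with the amount of distress in an arm

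*Protocol article*

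**What the plan says.** Section 2.5.2.3 of the protocol article defines the number of detected cases separately for each arm, at a threshold of VAS 6 or more in both.

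- **eHealth:** "The number of detected clinical cases: in the EG this will be obtained through the number of potential clinical cases recorded throughout treatment". The thermometer behind this is one "which will be scheduled weekly on the ICOnnecta't platform".
- **Control:** "In CG it will be obtained through the number of clinical cases recorded in the follow-up of face-to-face visits", or after a patient telephones to report a worsening and the visit is brought forward. On sessions, section 2.6.2 states: "This will consist of an average of seven individual sessions", spaced 2–3 weeks apart.

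Section 2.9 fixes the analysis: "Mean differences in the number of clinical cases detected (according to the emotional thermometer), waiting time to provide care" and the number of cases solved are compared between groups by Student t-tests. Neither section sets the count against a number of distressed patients, applies one reference standard to both arms, or counts missed cases.

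The HADS is a primary outcome (2.5.1, where a total of 10 or more marks moderate distress). The main outcomes are collected in both arms at T0 to T3 (2.1, 2.4), and the HADS is tested for non-inferiority at T2 and T3 (2.9). It is not linked to the detection outcome.

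The aims in section 1.1 state that "the cases at risk of emotional distress will be detected earlier than treatment as usual". The hypotheses there speak of time to detection, intervention and resolution, and expect equivalent emotional distress in the two arms.

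**The concern.** The count mixes two quantities: how much distress arises in an arm, and how much of it is found. Randomisation balances patients at baseline, but these cases arise afterwards, under treatments that are meant to change distress. Using the same case definition and the same screening frequency in both arms would not remove the problem.

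The other two outcomes in section 2.5.2.3 do not fill the gap. Waiting time starts only once a case has been flagged (eHealth) or confirmed (control), and the percentage resolved is built on clinical cases. A distressed patient who is never recorded enters none of the three. If distress differs between arms, the test on the count could be read as evidence about detection when it is partly or wholly evidence about distress.

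**Working it through.** The protocol gives no expected figure for the detection outcome, so there is none to reproduce. The planned 76 per arm and 25% dropout come from section 2.7. All prevalences, episode rates and detection shares below are assumptions for illustration.

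**1. Structure.** Expected detected cases = cases occurring × share detected.

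**2. Episodes per patient.** Evaluable patients per arm: 76 × 0.75 = 57. With Poisson counts, SE = sqrt((mean₁ + mean₂)/57).

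- *Equal detection (60%), eHealth 3 episodes, control 2.* Means are 3 × 0.6 = 1.8 and 2 × 0.6 = 1.2. SE = sqrt(3.0/57) = 0.229, z = 0.6/0.229 = 2.62, p = 0.009. The count favours eHealth although detection is identical.
- *eHealth detects 90% of 1.2 episodes, control 60% of 2.* Means are 1.08 and 1.2. SE = sqrt(2.28/57) = 0.200, z = −0.12/0.200 = −0.60, p = 0.55. Better detection is hidden.
- *Sensitivity to the Poisson assumption.* If episodes cluster within patients so that the variance is twice the mean, the first example has SE = sqrt(6.0/57) = 0.324, z = 1.85, p = 0.06. The direction is unchanged and the evidence is weaker.

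**3. Patients per arm.** Detected = 76 × prevalence × sensitivity; missed = 76 × prevalence × (1 − sensitivity).

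| Prevalence eHealth / control | Sensitivity eHealth / control | Detected | Missed |
|---|---|---|---|
| 40% / 30% | 80% / 80% | 24.3 / 18.2 | 6.1 / 4.6 |
| 40% / 30% | 70% / 80% | 21.3 / 18.2 | 9.1 / 4.6 |
| 30% / 50% | 90% / 60% | 20.5 / 22.8 | 2.3 / 15.2 |

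In the second row eHealth detects a smaller share and misses twice as many, yet its count is higher. In the third row the better detector has the lower count.

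**4. Where the direction turns.** The eHealth count is higher only while its sensitivity, divided by control sensitivity, exceeds control prevalence divided by eHealth prevalence. That ratio is 0.30/0.40 = 0.75 in the first two rows, and would be 0.30/0.50 = 0.60 at 50% against 30%.

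**5. What a share would show.** Detected divided by true cases gives 80% against 80%, 70% against 80%, and 90% against 60% in the three rows, which are the differences of interest.

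**6. Missed cases over all patients are not enough.** This proportion is prevalence × (1 − sensitivity). At 80% sensitivity in both arms and 40% against 30% distressed, it is 8% against 6% although detection is equal. At 20% distressed with 60% found, against 40% distressed with 80% found, it is 8% in both although detection differs.

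**7. Number of looks.** Nine months of weekly screening is about 39 looks, against about 7 control sessions. A simulation with identical distress in both arms (mean VAS 3 to 4, between- and within-patient SD 1.5, week-to-week correlation 0.7, all assumed) flags 47–69% of patients at least once with weekly looks and 26–46% with seven visits. Any detection measure based on flags must allow for this.

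**The case against.** The strongest reply has four parts.

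- **Direction.** Nowhere does the protocol say that a higher count is a success. Its hypotheses concern earlier detection and shorter times. A reader might infer that the sponsor has committed to reading more cases as better, but that comes only from the early-detection heading and the between-arm test. This stands, and it limits the point to what the test can show.
- **Expected distress.** Section 1.1 expects equivalent distress, and section 2.1 disclaims superior efficacy. A difference is therefore possible, but it is not what the plan expects. This also stands. Equivalence is nevertheless what the trial sets out to test, so the detection comparison should not have to assume it.
- **HADS.** A reader might infer that the plan has nothing that could separate distress from detection. That goes too far. A material excess of distress under eHealth should appear in the HADS comparison at T2 and T3. What is missing is the link between the HADS and the case record.
- **Inputs.** The illustrations rest on chosen figures. Equal detection is unlikely given the different screening frequencies, and clustering weakens the p-value. This stands for the size of the effect, but not for the structure, which follows from the definition of the count.

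Unequal ascertainment (unconfirmed weekly flags against cases recorded at visits or after a call) is a further difficulty with the same outcome. It adds to this one and does not replace it.

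**Conclusion.** The point holds in a limited form. The t-test on the number of detected cases cannot by itself support a claim of better detection. If distress differs between arms, the count can favour the arm with more distress, provided its sensitivity is equal or only moderately lower (above 0.75 of the other arm's at 40% against 30% prevalence). It can equally hide better detection. Under the assumed inputs the spurious result reaches p = 0.009, or p = 0.06 with variance twice the mean.

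Two stronger readings are tempting and not supported. One is that a programme leaving patients more distressed would always look better at detection; a large enough loss of sensitivity reverses the count. The other is that the detection aims as a whole cannot be answered; the stated hypotheses concern time, which this point does not examine. The outcome is secondary, and the HADS non-inferiority conclusion is unaffected. The change is worth making because it is cheap and the data are already planned.

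**What to change.** In sections 2.5.2.3 and 2.9:

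1. Make the raw number of cases descriptive, with no claim of better detection.
2. As the detection comparison, report by arm the share of patients with HADS total of 10 or more at T1, T2 or T3 who had a clinical case recorded since the previous assessment. Use the scheduled HADS sent to both arms, not the HADS completed before eHealth sessions.
3. Beside it, show by arm the proportion of all assessed patients with HADS of 10 or more, and the proportion with HADS of 10 or more and no case recorded. State that the latter also depends on prevalence.
4. Show by arm the share of patients with HADS below 10 who were flagged, because weekly screening gives eHealth more chances of a flag (about 13 looks between assessments).

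The cost is wording in two sections and a few variables derived from the HADS and the case record. No visit, questionnaire or clinical procedure changes. Two downsides should be stated: the share is taken in a subgroup defined after randomisation, so the arms need not be comparable within it, and it covers distress only at the scheduled assessments.
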